### 2.9. Discontinuation of the Intervention

The intervention will be terminated in cases with severe adverse events, when participants wish to withdraw from the trial, or when patients use unpermitted medication that would interfere with the recovery outcomes. Patients will have the option to ask the doctor about possible alternative therapies (e.g., nutritional support such as use of tricreatine *β*-hydroxyl-methylbutyrate, antioxidant therapy, and immunoglobulin therapy).

### 2.10. Outcome Measures

#### 2.10.1. Baseline Information

Demographic information will be collected using a custom-made, standardized survey form that includes center location, name, age, gender, address, telephone number, and employment. Medical information will be collected using a custom-made form that records clinical information, including diagnosis, medication history, and APACHEII rating forms.

### 2.11. Primary Outcome Measures

The average change in the quadriceps femoris muscle area, thickness, vastus intermediate muscle thickness, subcutaneous tissue thickness, and ultrasonic intensity of the rectus femoris will be measured in a blinded manner, and the scores obtained at the baseline and at the end of the 4-week treatment will be compared for each group.

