## Abstract

To evaluate the efficacy of acupuncture combined with rehabilitation training in patients with intensive care unit (ICU)-acquired muscle weakness (ICUAW), a single-blinded, randomized, sham-controlled clinical trial is designed for execution. In total, 56 participants with ICUAW will be randomly assigned to the treatment and control groups with 28 participants in each group. The participants will be treated with acupunctures or sham procedures at LI15, LI11, ST36, GB34, and ST31, 5 times per week for a total of 20 sessions in 4 weeks while they will receive rehabilitation training. Patients will be followed up every month for 3 months after treatment. The primary outcomes include changes in quadriceps femoris muscle area, thickness, vastus intermediate muscle thickness, subcutaneous tissue thickness, and ultrasonic intensities of the rectus femoris. The secondary outcomes consist of the modified Barthel index score and the Medical Research Council total score. Participants' mechanical ventilation, the rate of detachment at the second week, the 28-day survival rate, and the occurrence of adverse reactions will be measured, and any side effects will be reported and recorded. Patient outcomes between the treatment and control groups will be compared and statistically tested. We anticipate that the therapeutic regimen of acupuncture combined with rehabilitation training would be more effective than the rehabilitation training alone for the treatment of the ICUAW. The findings of this study could help develop a better strategy for the treatment of the ICUAW disease and explore a clinical application of an acupuncture technique. Trial registration: Chinese Clinical Trial Register ChiCTR2000038779. Registered 30 September, 2020, https://www.chictr.org.cn/showproj.aspx?proj=62284.

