### 2.18. Statistical Analysis

#### 2.18.1. Sample Size Calculation

The trial will test two groups in parallel. The sample size calculation will be performed using the software SAS (version 9.3, SAS Institute Inc., Cary, NC, USA). The mean change in the primary outcome before and after treatment will be used as the indicator of efficacy evaluation in the calculation of the sample size. The results of previous studies yielded a mean ultrasound measurement of muscle thickness change of 0.45 ± 0.1 [25] and a mean ultrasonic intensity of muscle change of 25 ± 3 [26] after the loss of muscle mass and function. To detect a significant difference with a power of 80%, an alpha value of 0.05, and an acceptable delta value of 0.2, a sample size comprising at least 23 participants in each group will be needed. We have added an additional five patients per group considering a possible 20% dropout.

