### 2.21. Efficacy Analysis

Efficacy data analyses will be conducted based on the intention-to-treat population. All participants will be initially included in one of the two groups and considered in the statistical analyses. Analysis of efficacy will be conducted for each protocol and include all the participants who would complete the entire research processing. Descriptive statistics will be used to report primary outcome indicators between the two groups. All the data will be statistically analyzed using SPSS. All measurements will be expressed as mean ± standard deviation. The *t*-test will be used for comparisons between two samples if the distributions are normal, and the F-test will be used for comparisons among multiple samples. The Kruskal–Wallis H-rank sum test was used if the distribution is not normal. The participants' sex and course of disease will be recorded, and the data will be tested using the *χ*^2^ test. The ultrasound data will be analyzed by a mixed-effect model. The Cox-regression analysis will be performed to identify outcome-related factors. *P* < 0.05 will be considered as statistically significant.

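### Five unranked primary outcomes, a single 0.05 threshold and a sample size built for one primary outcome: the stated 5% error does not hold for the overall primary claim

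*Protocol article*

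**What the plan says.** The Abstract states: "The primary outcomes include changes in quadriceps femoris muscle area, thickness, vastus intermediate muscle thickness, subcutaneous tissue thickness, and ultrasonic intensities of the rectus femoris". Section 2.11 (Primary Outcome Measures) lists the same five, "The average change in the quadriceps femoris muscle area, thickness, vastus intermediate muscle thickness, subcutaneous tissue thickness, and ultrasonic intensity of the rectus femoris", and fixes the time point: "the scores obtained at the baseline and at the end of the 4-week treatment will be compared for each group". That makes five primary comparisons at one time point, with no lead measure, no order and no rule on whether one, several or all must be positive.

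Section 2.21 (Efficacy Analysis) gives one threshold for everything: a P value below "0.05 will be considered as statistically significant". It lists t-tests, F-tests, a rank test and a mixed-effect model for the ultrasound data.

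Section 2.18.1 (Sample Size Calculation) refers to the primary outcome in the singular. Its specification is: "To detect a significant difference with a power of 80%, an alpha value of 0.05, and an acceptable delta value of 0.2". It cites planning values for two quantities only: "a mean ultrasound measurement of muscle thickness change of 0.45 ± 0.1", and an ultrasonic intensity change of 25 ± 3. Area, vastus intermedius thickness and subcutaneous tissue thickness have none.

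Section 2.23 announces a separate, fully specified statistical analysis plan, which is not available here.

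**The concern.** A trial sized for one test at 0.05 keeps its 5% error only if one test decides the result. Here five measures hold equal primary status, and nothing in the text stops a significant result on any one of them from being reported as a positive primary outcome. The alpha in section 2.18.1 would then describe each single comparison and not the trial's primary conclusion.

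The direction of benefit adds to this. No direction is stated for any of the five. For muscle area and thickness it can be inferred from the Introduction, which describes acupuncture as alleviating atrophy. For subcutaneous tissue thickness, which is not a muscle measure, nothing in the article says which change would be an improvement.

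What is at stake is how far the main claim can be trusted. The Discussion expects the completed trial to give strong evidence for the combined regimen, and it would rest on 56 patients with five possible routes to a positive primary result.

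**Working it through.** **Inputs.** From the article: five primary measures at one time point (2.11), threshold 0.05 (2.21), and alpha 0.05, power 80%, delta 0.2 and 23 per group (2.18.1). Assumed, because the article does not say: two-sided tests between groups, success if any one measure is significant, and a common correlation rho between the five test statistics.

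**The plan's own figure.** The article states no error rate for the five measures together, so the figure to reproduce is 23 per group. Use n = 2(1.960 + 0.842)² × (SD/delta)² = 15.70 × (SD/delta)².

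- Thickness, delta 0.2, SD 0.1: 15.70 × 0.25 = 3.9, so 4 per group (6 by exact t-test).
- Intensity, delta 0.2, SD 3: 15.70 × 225, so about 3,532 per group.
- Delta read as 20% of the thickness mean (0.09, SD 0.1): 15.70 × 1.235 = 19.4, so 20 (21 by exact t-test).

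None gives 23. That is a separate matter, and the error rates below do not depend on it. What matters here is that the calculation spends the whole 0.05 on one comparison.

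**Chance of at least one false significant result, no true effect on any measure.** If the tests are independent:

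- either direction: 1 − 0.95⁵ = 22.6%
- favouring acupuncture only, with a direction fixed for all five: 1 − 0.975⁵ = 11.9%, against 2.5% for one test

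For correlated statistics, by simulation of five equally correlated normal statistics (400,000 draws):

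| rho (assumed) | Either direction (nominal 5%) | Favouring acupuncture (nominal 2.5%) |
|---|---|---|
| 0 | 22.6% | 11.9% |
| 0.3 | 21.0% | 10.6% |
| 0.5 | 18.3% | 9.1% |
| 0.7 | 14.9% | 7.4% |
| 0.8 | 12.7% | 6.4% |
| 0.9 | 10.2% | 5.1% |

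Simulated t-tests with 23 and 28 per group agree: 22.1% and 22.9% at rho 0, 15.1% and 14.8% at rho 0.7 (either direction).

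**A less uniform correlation pattern.** With the three muscle-size measures correlated 0.7 to 0.9 and all other pairs 0 to 0.5, the rate is 15.2% to 18.8% in either direction and 7.5% to 9.6% favouring acupuncture.

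**Direction open for one measure.** If only subcutaneous tissue thickness can count either way, independence gives 1 − 0.975⁴ × 0.95 = 14.1%; at rho 0.7 it is 9.9%. The nominal rate lies between 2.5% and 5%.

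**Other success rules.** One named primary outcome gives 5%. Requiring all five to be significant gives at most 5%. Testing each at 0.05/5 = 0.01 gives at most 1 − 0.99⁵ = 4.9% if independent, and less under positive correlation.

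**The case against.** A reader might infer that the chance of a false positive efficacy claim is simply 15% to 23%. The article does not support that, for three reasons. First, the figure counts significance in either direction, including results favouring sham, which nobody would report as efficacy. Second, it leaves out correlations above about 0.7. Area, quadriceps thickness and vastus intermedius thickness overlap as size measures of one muscle group, so independence is the least plausible end. Third, it takes an any-one-succeeds rule as given, when the article states no rule. An all-five rule would hold the error at or below 5%. These objections stand, and the range has to be given with its assumptions.

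It is also fair that the wording in section 2.11 (a comparison for each group) could mean within-group tests, and that section 2.21 speaks of describing the primary indicators between groups. The between-group reading is the natural one, since the Abstract says outcomes will be compared between the treatment and control groups, but it is a reading.

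A further objection is that adjustment for multiple tests commonly sits in the analysis plan, which is not shown. That holds for the mechanics, and the absence of a named adjustment is not the point. The point is what the protocol itself fixes: five equal primaries beside a sample size for one, at full alpha. An analysis plan that split alpha would change the significance level on which the power in section 2.18.1 is stated.

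Finally, a reader might argue that a Bonferroni split would cut power from 80% to 57%. The arithmetic is right for 23 per group and a standardized effect of 0.845. But that effect is solved back from the 23 per group and does not appear in the article. With the thickness values as printed (0.2/0.1 = 2), power at 0.01 would exceed 99.9%. The document therefore does not show how much power an adjustment would cost.

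**Conclusion.** The point holds in this form. The protocol names five primary measures without rank or success rule, applies a single 0.05, and sizes the trial on one primary outcome at undivided alpha. If any one significant measure counts as success and the tests are two-sided between groups, the error is about 10% to 23% in either direction, or about 5% to 12% favouring acupuncture against a nominal 2.5%, for correlations between 0.9 and 0. The correlations and the success rule are assumptions. On either count the error is at least about twice nominal across that range, so the 0.05 in section 2.18.1 does not hold for the overall primary claim. Confidence is high that the sections conflict and lower on the exact size, because the success rule that would settle it is not stated.

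**What to change.** Before unblinding, name one of the five as the single primary outcome at week 4 and make the other four secondary. State the direction of benefit for each, including subcutaneous tissue thickness. Muscle thickness is a natural candidate because section 2.18.1 already gives a planning value for it, but the choice is the sponsor's. Align the Abstract, section 2.11, section 2.18.1 and the registry entry.

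If several primaries are kept, test them with Holm, say so in section 2.21, and restate the power in section 2.18.1 at the adjusted alpha (0.01 at the first step with five).

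The cost is wording only: every measurement and visit stays. The sponsor gives up claiming success on whichever measure turns out significant or, under Holm, accepts a lower stated power per measure.

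### The primary outcome is worded as a before-after comparison within each arm and its between-group report as descriptive, contradicting the between-group test promised in the Abstract

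*Protocol article*

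**What the plan says.** Section 2.11 (Primary Outcome Measures) gives the outcome as "The average change in the quadriceps femoris muscle area, thickness, vastus intermediate muscle thickness, subcutaneous tissue thickness, and ultrasonic intensity of the rectus femoris" and the comparison as follows: "the scores obtained at the baseline and at the end of the 4-week treatment will be compared for each group". No contrast between acupuncture and sham appears in that section.

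Section 2.21 (Efficacy Analysis) has one sentence that names the primary outcome in relation to the two arms: "Descriptive statistics will be used to report primary outcome indicators between the two groups". The same section also lists inferential methods. It provides for a t-test, saying that this "test will be used for comparisons between two samples if the distributions are normal", for a Kruskal–Wallis test if they are not, and for a model: "The ultrasound data will be analyzed by a mixed-effect model". The t-test is attached to no named outcome, and the model sentence names no treatment contrast.

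The Abstract says: "Patient outcomes between the treatment and control groups will be compared and statistically tested". It anticipates that "acupuncture combined with rehabilitation training would be more effective than the rehabilitation training alone for the treatment of the ICUAW". Section 2.18.1 describes two parallel arms and says: "The mean change in the primary outcome before and after treatment will be used as the indicator of efficacy evaluation".

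**The concern.** Randomising against sham serves to separate the effect of needling from everything else that changes over four weeks. Here that is a great deal. Section 2.2.6 gives rehabilitation training to every participant, and the Introduction describes recovery from ICUAW over weeks to months. Muscle measures may therefore change in both arms with no acupuncture effect at all.

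A comparison of baseline with week 4 inside one arm tests whether anything changed in that arm. It does not test the hypothesis in the Abstract. If section 2.11 is followed as written, a before-after result in the acupuncture arm can be reported as the prespecified primary result. A contrast of the form *significant here, not significant there* can also be presented as if it compared the arms. Either use gives up the randomised comparison.

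**Working it through.** **1. The statements side by side (Protocol article).**

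| Place | Comparison of the primary outcome |
|---|---|
| Abstract | Between groups, statistically tested; comparative hypothesis |
| 2.11 | Baseline versus week 4, within each arm |
| 2.18.1 | Two parallel arms, sized on mean change |
| 2.21, sentence naming the primary outcome | Between groups, descriptive |
| 2.21, t-test | Two samples, no outcome named |
| 2.21, mixed-effect model | Ultrasound data, no contrast named |

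The two sentences that name the primary outcome and say how it is compared or reported (2.11 and the descriptive sentence in 2.21) do not match the Abstract. The sentences that could supply a between-group test do not say that they do so for the primary outcome.

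**2. What each comparison tests.** Let C be the mean change common to both arms (recovery plus rehabilitation) and A the added effect of acupuncture. The expected change is C + A in the acupuncture arm and C in the sham arm. The within-arm test addresses C + A = 0. The between-group test addresses (C + A) − C = A = 0. If A = 0 and C is not zero, the within-arm test rejects at the rate of its power to detect C.

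**3. Size, for one measure.** The plan gives no figure on this point to reproduce.

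Inputs:
- n = 23 per arm, the number in section 2.18.1 before the dropout allowance. It is used here only as the arm size; its derivation is not examined.
- Two-sided α = 0.05. The document gives 0.05; two-sided is an assumption.
- A = 0, independent arms and equal within-arm power.
- A common standardised change d (mean change divided by the SD of change) of 0.2, 0.5 or 0.8. This is an assumed range, not taken from the document.
- An assumed decision rule that the protocol does not state: claim efficacy if the acupuncture arm is significant and the sham arm is not.

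Formulas: p is the power of a paired t-test with 22 degrees of freedom and noncentrality d√23. The false-claim rate is p(1 − p).

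| d | d√23 | p (acupuncture arm significant, A = 0) | p(1 − p) |
|---|---|---|---|
| 0.2 | 0.96 | 0.151 | 0.151 × 0.849 = 0.128 |
| 0.5 | 2.40 | 0.630 | 0.630 × 0.370 = 0.233 |
| 0.8 | 3.84 | 0.956 | 0.956 × 0.044 = 0.042 |

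The product p(1 − p) is largest at p = 0.5, where it is 0.25. The benchmark is 0.05/2 = 2.5%, the rate of a false claim in favour of acupuncture from a two-sided 5% between-group test.

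The column for p shows the cruder misuse, in which a significant change in the acupuncture arm is itself read as efficacy. With no acupuncture effect this happens 15%, 63% and 96% of the time at the three values of d.

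**The case against.** A reader might infer that the between-group comparison is only descriptive throughout, and that the plan never tests acupuncture against sham. The document does not support that. Section 2.21 does not restrict the between-group report to description. It goes on to list a two-sample t-test and a mixed-effect model for the ultrasound data, and all five primary measures are ultrasound data. Section 2.18.1 sizes two parallel arms, section 2.20 plans baseline-adjusted analyses, and the Abstract states the comparative intent outright. Section 2.11 names no paired test and no rule for success.

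It can also be said that the false-claim rates depend on an assumed rule and an assumed change. If both arms change strongly, the rate falls to about 4% at d = 0.8, so a general statement that the error is far above 5% would be wrong. Finally, section 2.23 announces a separate statistical analysis plan, and the terms of the mixed model may properly sit there.

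All of this stands, and it limits the point to a contradiction. It does not remove it. The literal wording of 2.11 is within-arm, the descriptive sentence in 2.21 is the only one there that names the primary outcome, and a mixed-effect model can report changes over time within each arm as readily as a treatment contrast. What is at issue is what this document states, not detail it leaves to the later plan.

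**Conclusion.** The point holds as an internal contradiction that should be corrected. Sections 2.11 and 2.21, read as worded, put the primary comparison within arms and the between-group report under description, while the Abstract promises a between-group test of a comparative hypothesis. The between-group intent and a suitable model are both in the document, but neither is tied to the primary outcomes as an acupuncture-versus-sham contrast.

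The size is conditional. Under the assumed rule, with no true difference, equal within-arm power and 23 per arm, the false-claim rate for one measure is about 13%, 23% and 4% at the assumed changes and at most 25%, against 2.5%. The conclusion that a within-arm change cannot be attributed to acupuncture does not depend on these figures. It follows from rehabilitation in both arms and expected recovery.

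**What to change.** Reword sections 2.11 and 2.21 to agree with the Abstract. Suggested text: *For each primary ultrasound measure, the primary analysis is the between-group difference (acupuncture minus sham) in change from baseline to week 4, with 95% confidence interval and two-sided p-value, from the mixed-effect model adjusted for the baseline value of that measure. Within-group changes are reported as supportive description and are not the basis for an efficacy claim.* The descriptive sentence in 2.21 should then be limited to summary statistics that accompany this analysis.

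The cost is wording only. The model is already named in 2.21, baseline-adjusted analyses are planned in 2.20, and Table 1 schedules all five measures at W0 and W4. No added patients or visits are needed. The rewording applies to each measure in turn; it does not settle how results on five primary measures combine into one efficacy claim, which is a separate matter.

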### 2.12. Secondary Outcome Measures

The average change in quadriceps femoris muscle area, thickness, vastus intermediate muscle thickness, subcutaneous tissue thickness, and ultrasonic intensity of the rectus femoris will be measured, and the scores obtained at the baseline, 2 weeks, and 3 months after the last treatment will be compared. MBI and MRC scores will be evaluated at 2 weeks, 4 weeks, and 3 months after the last treatment. The participants' mechanical ventilation, rate of detachment at the second week, 28-day survival rate, and occurrence of adverse reactions will be evaluated, and any noticed side effects of the treatment will be recorded. All outcome readings will be scored on quantitative scales and presented as mean values and standard deviations.

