## 1. Introduction

The intensive care unit (ICU)-acquired weakness (ICUAW) is a generalized muscle weakness complication developed during ICU admissions for which no other disease cause can be identified except for acute illness or its treatment. Approximately 40% of ICU patients with a history of at least 48 h of mechanical ventilation develop ICUAW. The disease affects peripheral and respiratory muscles, causing prolonged time of mechanical ventilation and hospital stay, increased hospital mortality, and chronic disability [1–5]. The mechanisms by which ICUAW develops are complex and involve functional and structural alterations in both the muscles and the nerves. Recovery from ICUAW typically takes several weeks or months, and muscle weakness in some patients can last for up to 2 years after discharge from the ICU. Because the pathogenesis of ICUAW is still unclear, there are no specific treatments. The current management of ICUAW includes an active treatment of the primary disease (e.g., sepsis), prevention of infection, control of high blood sugar, reduction of the duration of immobilization, and avoidance of other known risk factors, such as malnutrition, unnecessary application of corticosteroids and neuromuscular blockers, and early rehabilitation [6–8]. Thus, the development of easy-to-perform, more effective ICUAW-targeted interventions is needed for the prevention and treatment of ICUAW.

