Acupuncture is a component of the traditional Chinese medicine that is practiced in China as well as abroad as a part of medical care for systemic disease treatment and is believed to work on the principle of the redistribution of “QI,” the life energy concept in Chinese. As per traditional Chinese medicine, diseases result from an imbalance or poor flow of QI. Acupuncture can cure the diseases based on the conduction of meridians and acupoints and following the application of certain operations to improve the flow of QI. In our previous studies, we found that ICU-acquired myasthenia is an acute polyneuromyopathy, and early rehabilitation exercise alone can only reduce physiological dysfunction. Based on our clinical experience on the treatment of various neuromyopathy diseases, we found that acupuncture therapy can improve patients' nerve function [9], restore their muscle atrophy [10] and muscle mass and strength [11], relieve their symptoms, shorten offline time and hospital stay, and improve the quality of patients' lives. In particular, it can significantly alleviate the obvious atrophy of lower limb muscle thickness and cross-sectional area of ICU patients with acquired muscle weakness [12, 13]. More recent studies have found that the combination of acupuncture and speech rehabilitation training improved the total response rate of stroke patients with dysarthria [14]. Based on these studies, we presume that acupuncture and moxibustion combined with rehabilitation training can synergize the effects and offer complementary advantages. The combined therapeutic strategy is superior to simple acupuncture and rehabilitation training alone for the prevention and treatment of patients with ICUAW. However, the efficacy of this therapeutic regimen has not been evaluated yet. To test this hypothesis, we designed a randomized controlled trial with a 3-month follow-up to evaluate whether acupuncture combined with rehabilitation training benefits the recovery of patients with ICUAW and planned to determine the temporal extent of this effect after last successful treatment.

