#### 2.2.6. Acupuncture and Sham Therapy

All research assistants and licensed acupuncturists involved in the trial will receive a 2-day training prior to the onset of the study. Both treatments will consist of 20 sessions over 4 weeks, 5 times per week, and each for 30 min. We plan to treat the patients for 4 weeks because normally our patients would have stayed in ICU for 4 weeks. Briefly, patients will be asked to lie down in a supine position. After sterilization, the 0.25 × 40 mm acupuncture needles (Suzhou Tianxie Acupuncture Instruments Co., Ltd., Suzhou, China) will be inserted to the acupoints of the Jianyu (LI15), Quchi (LI11), Zusanli (ST36), Yanglingquan (GB34), and Biguan (ST31) using a neutral reinforcing and reduced manipulation technique. Each needle will be rotated until the patient experiences the “QI” feeling of soreness, heaviness, and the sensation of distension. The procedure for conducting will be standardized as shown in Table 2. Participants in the control group will receive sham needling at the same acupoints with nested blunt needles. All the procedures will remain the same as the one in the treatment group with the exception of the needles, which will be forced to pierce the fixed pad and reach the skin surface without penetrating the skin. All participants will receive regular rehabilitation training.

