### 2.8. Concomitant Care and Intervention

Participants with severe symptoms in both groups will be treated by first-aid kit medications. The type of medicine, dosage, and usage will be recorded on diary cards for analyses. For those with more complicated chronic diseases who must continue to take their routine medication and receive the necessary therapies, the names of the diseases, medications, and therapies used will be recorded.

Our registered nurses will monitor all the patients in the ICU 24 h/day, 7 days/week, and our ICU physicians will examine the patients every 6 h. In case the acupuncture causes hemodynamic instabilities, such as arrhythmias, hypotension, and confusion, the ICU physicians will be called immediately to treat the patients. In most cases, hemodynamic instability would require some type of artificial, mechanical support to maintain the blood pressure and heart activity. For cases in which the participants are unable to receive additional intervention with acupuncture rehabilitation after an evaluation, the participants will be withdrawn immediately from the study and undergo an alternative rehabilitation program. Based on our clinical experience, it is unlikely that patients will have sudden disorders of consciousness or limb twisting; these symptoms are usually experienced by patients suffering from seizures. If such problems arise in Grade I or II sectors of rehabilitation training, the patients will be kept away from the unsafe area and will be allowed to lie on their backs by removing the pillows. Any secretions from the mouth will be removed by turning the patients' heads to one side. Furthermore, ICU doctors will be called to rescue the patients and obtain neurological consultation.

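### The only weaning outcome with a defined time point is a yes/no rate at week 2, halfway through treatment; time to detachment through day 28 would fit the rationale better and cost little.

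*Protocol article*

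**What the plan says.** Section 2.12 (Secondary Outcome Measures) names "The participants' mechanical ventilation, rate of detachment at the second week, 28-day survival rate", and the Abstract gives the same list. The first item has no stated quantity or time point. The second is a proportion at week 2. The same section says that all outcome readings will be scored on quantitative scales and shown as means and standard deviations.

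Other parts of the article bear on this choice:

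- Inclusion criterion 5 (section 2.2.1) requires mechanical ventilation, so weaning concerns all 56 participants.
- Section 2.2.6: "Both treatments will consist of 20 sessions over 4 weeks, 5 times per week". The length is chosen because "normally our patients would have stayed in ICU for 4 weeks".
- The Introduction describes the disease as "causing prolonged time of mechanical ventilation and hospital stay" and credits acupuncture with the ability to "shorten offline time and hospital stay". The Discussion adds that it helps weaning from prolonged ventilation.
- Section 2.11 judges the primary ultrasound outcomes at the end of the 4 weeks.
- Section 2.21 names Cox regression, but only to look for factors related to outcome.
- Table 1 has no row for ventilation.

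**The concern.** Detachment from the ventilator is an event in time. A yes/no reading at week 2 scores day 2 and day 14 alike, and scores day 15 the same as never. At five sessions a week, week 2 comes after 2 × 5 = 10 of the 20 sessions, so weaning achieved in the second half of treatment counts as failure. The primary outcomes are read after the full course; weaning is read halfway.

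Nothing in the article explains the cut. Survival is followed to day 28, the usual ICU stay is given as 4 weeks, and section 2.8 says "Our registered nurses will monitor all the patients in the ICU 24 h/day, 7 days/week", so the detachment date should be known to staff.

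Two things are at stake: power in a trial with 28 per arm, and interpretation. A null result at week 2 could be taken as no effect on weaning when half the treatment had not been given.

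**Working it through.** **The plan's own figure.** There is none to reproduce. The sample size in section 2.18.1 rests on ultrasound measures, and no weaning rate, effect or power is stated. Everything below except the group size is therefore an assumption.

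**Inputs**

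- 28 per arm, from the Abstract.
- Two-sided alpha 0.05 (assumed; section 2.18.1 gives 0.05 without sidedness).
- Control probability *p* of detachment by day 14, with death ignored: 30-60% (assumed).
- Ratio of detachment rates, RR: 1.5-2.5, constant over time (assumed).
- Mortality by day 28: 20% in both arms, or none (assumed).
- Chi-square test for the week-2 proportion (assumed; section 2.21 does not name the test for this outcome).

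**Model.** Exponential times. The control daily rate is −ln(1 − *p*)/14, so the treated probability by day 14 is p₁ = 1 − (1 − *p*)^RR.

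**Detachments the week-2 rate does not see.** The share of control detachments by day 28 that fall in weeks 3-4 is 1 − *p*/[1 − (1 − *p*)²]. With no deaths this is 41% at *p* = 30%, 33% at 50% and 29% at 60%.

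**One case by hand, no deaths, *p* = 50%, RR 2.0**

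- p₁ = 1 − 0.5² = 75%.
- Week-2 proportion, 50% vs 75%: z = [0.25√28 − 1.96√(2 × 0.625 × 0.375)]/√(0.25 + 0.1875) = (1.323 − 1.342)/0.661 = −0.03, so power is about 49%.
- Time to detachment: expected events by day 28 are D = 28 × [(1 − 0.5²) + (1 − 0.5⁴)] = 28 × 1.6875 = 47.25. Schoenfeld power = Φ(√47.25/2 × ln 2 − 1.96) = Φ(0.42), about 66%.
- The gain is 17 points. Simulation gives 66% vs 49%.

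**Simulated power, 28 per arm** (4,000 trials per row; with deaths, patients who die before detachment stay in the risk set as never detached, which corresponds to the Gray test)

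| *p* | RR | No deaths: week 2 / day 28 (gain) | 20% deaths: week 2 / day 28 (gain) |
|---|---|---|---|
| 30% | 1.5 | 15% / 21% (+6) | 14% / 18% (+5) |
| 30% | 2.0 | 35% / 55% (+20) | 34% / 48% (+14) |
| 30% | 2.5 | 58% / 79% (+22) | 56% / 73% (+16) |
| 50% | 1.5 | 19% / 28% (+9) | 18% / 24% (+6) |
| 50% | 2.0 | 49% / 66% (+17) | 46% / 56% (+10) |
| 50% | 2.5 | 75% / 89% (+14) | 71% / 79% (+8) |

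Gains are computed before rounding. At *p* = 60% with 20% deaths, a separate simulation of the same model (1,500 trials per setting) gives 51% / 58% at RR 2.0; the smallest gains, about 3-4 points, are at *p* = 60% and RR 1.5. The range with deaths is thus roughly 3-16 points.

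**Sensitivity**

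- If the effect starts only after week 1 (RR 2.0, 20% deaths, *p* = 30% or 50%), power is 14-15% for the week-2 rate and 23-25% for the day-28 comparison.
- With Fisher's exact test in place of chi-square, the gaps in the right-hand column widen to about 10-27 points.

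**Does the other listed item repair this?** Suppose mechanical ventilation means days on the ventilator, shown as mean and SD and compared by the *t*-test or rank test of section 2.21. The article then gives no rule for death before weaning or for patients still ventilated. A patient who dies early while ventilated would contribute a short, apparently favourable duration.

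**The case against.** The strongest reply is that timing may not be lost at all. Mechanical ventilation is listed as its own item before the week-2 rate, section 2.12 says outcomes are quantitative, and duration is a natural reading. Cox regression, which needs event times, is also named. The article condenses a fuller protocol, and section 2.23 promises a separate analysis plan. A reader might infer that the trial discards all timing of weaning; the article does not establish that, and the missing definition alone is not the finding. What remains is the explicit week-2 measure, stated in both the Abstract and section 2.12. Cox regression is not tied to weaning or to the comparison between arms.

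Second, the time-based statements in the Introduction describe disease burden and earlier experience, not this trial's hypothesis, which is about recovery. That is fair. They are still the grounds offered for expecting a benefit, and a week-2 proportion captures them only in part.

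Third, week 2 is a scheduled assessment, so the cut is not arbitrary. Week 4 is scheduled too, and the primary outcomes are read there.

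Fourth, weaning is one of several secondary outcomes and the trial is not sized for it. This stands, and it limits the weight of the point.

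**Conclusion.** The point holds in a limited form. The one weaning measure with a fixed time point is read at mid-treatment, ignores when detachment occurs, and treats detachments in weeks 3-4 as failures. A day-28 time-to-detachment comparison with death as a competing event would gain roughly 3-16 points of power with 20% mortality, and up to about 20 with no deaths, for control week-2 rates of 30-60% and rate ratios of 1.5-2.5.

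These figures rest wholly on assumed rates, a constant rate ratio and the chosen tests. A reader might take them as a known loss in this trial; the protocol gives no weaning inputs, so they are only an illustration of size. Nor would the change make the trial adequate for weaning: at a rate ratio of 1.5, power stays at about 18-24% with 20% deaths in the tabulated cases, and at 28% or less without. The primary ultrasound conclusion is not affected. The change is worth making because it is cheap and gives a better-matched endpoint.

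**What to change.** In section 2.12, make the tested weaning outcome the time from randomisation to ventilator detachment through day 28. Compare the arms by cumulative incidence, with death before detachment as a competing event (Gray test or Fine-Gray model). Record the detachment date, and prespecify a definition of detachment that covers re-ventilation. Keep the week-2 proportion as a descriptive value read from the same curve. State what the separate mechanical ventilation item measures, or fold it into this outcome.

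The cost is one date field on the case report form, one definition and some wording here and in the analysis plan. No patients, visits or procedures are added. The small downside is that a competing-risk summary is slightly harder to explain than a single percentage.
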